# SYNOPSIS

| Study Title | **A pilot study of adjunctive aspirin for the treatment of HIV negative adults with tuberculous meningitis** |
| --- | --- |
| Internal ref. no. | 23TB |
| Clinical Phase | Phase II |
| Trial Design | Double blind, 1:1:1 randomized placebo controlled trial |
| Trial Participants | Adults with tuberculous meningitis |
| Planned Sample Size | 120 patients |
| Follow-up duration | 240 days |
| Planned Enrolment Period | September 2014 to December 2016 |
| Primary Objective | To generate pilot data on the safety and efficacy of 81mg daily and 1000mg daily dose adjunctive aspirin. |
| Secondary Objectives | To determine whether host genotype influences any of the above effects  To determine whether innate host macrophage antimicrobial activity influences outcome  To assess the plasma pharmacokinetics of aspirin |
| Primary Endpoint | Primary safety endpoint: Clinically significant upper gastro-intestinal or cerebral bleeding by 60 days  Primary efficacy endpoint: New MRI-proven brain infarction or death by 60 days |
| Secondary Endpoints | Time to death during 240 days  Neurological disability by 60 days and 240 days  Duration of hospital stay  Grade 3&4 and serious adverse events by 60 days  The proportion of patients with MRI-proven infarction by day 240  Antimicrobial activity of peripheral blood monocyte/macrophages on day 30 and 60 compared to baseline  Concentration-time profile of salicylic acid including exposure, peak levels, half-life, elimination clearance and volume distribution |
| Investigational Medicinal Products | Aspirin and placebo |
| Form | Tablet |
| Dose | 81mg,1000mg or placebo daily for 60 days |
| Route | Oral/nasogastric tube (if unable to swallow safely) |

#

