# OBJECTIVES

## Primary Objective

To generate pilot data on the safety and efficacy of 81mg daily and 1000mg daily dose adjunctive aspirin compared to no aspirin.

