## Primary and Secondary Endpoints/Outcome Measures

The primary safety endpoint will be the occurrence of clinically significant upper-gastro-intestinal bleeding and any cerebral bleeding confirmed by brain imaging by 60 days from randomisation.

Clinically significant upper gastro-intestinal bleeding will be defined as any one of the following:

1. Vomiting fresh or changed blood of any volume
2. Melena
3. Unexplained drop in haemoglobin concentration of >2g/L
4. Greater than 5mls of fresh or changed blood aspirated from nasogastric tube

The primary efficacy endpoint will be any new MRI-proven brain infarction or death by 60 days. To assess this endpoint MRI will need to be taken at baseline and at 60 days from randomisation. The scans will be read by an independent neuroradiologist blind to the treatment allocation.

The secondary endpoints will be:

- Number of grade 3&4 and serious adverse events by day 60 from randomisation
- Time to death during 240 days from randomisation
- Duration of hospital stay
- Neurological disability (as assessed by the modified Rankin score and Glasgow outcome score) by days 60 and 240.
- Resolution of CSF inflammation by day 30 through measurement of CSF leucocytes, protein, glucose, cytokines (TNF-α, IL-1β, IL-8, IL-10, IFNγ) and eicosanoids (15-epi-Lipoxin, Lipoxin A4, LTB4, PGE2, TBXB2, PGD2).
- Antimicrobial activity of peripheral blood monocyte/macrophages on day 240 compared to baseline.
- The proportion of patients with MRI-proven infarction by day 240
- Concentration-time profile of salicylic acid including exposure, peak levels, half-life, elimination clearance and volume distribution

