## Adverse Event Recording

All adverse events which initiate after administration of the first dose of study drug and before the end of study day 60 will be recorded in the CRF. Events which are grade 3 and 4 adverse events and those judged to be possibly related or related to the trial intervention will be followed to resolution.

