## Regulatory Reporting of Adverse Events

As serious adverse events and mortality are common in tuberculous meningitis, safety reporting will focus on events of potential relevance to the trial intervention. The following events will be reported to the site ethical committee and the ethical committee of the Viet Nam Ministry of Health:

- All unexpected serious adverse events
- All serious adverse events judged to be related or possibly related to the trial intervention
- All deaths

Reporting to the ethical committees will include an initial written report, which will be sent as soon as possible and within 7 days of occurrence. The format and content of the initial report should follow the Viet Nam Ministry of Health report template and include all information available at the time of reporting. A follow up report with complete details will be sent within 15 days of the initial report if the initial report does not contain the details of event resolution.

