## Description of Statistical Methods

The risk of clinically significant upper-gastro-intestinal bleeding and image-proven cerebral bleeding by 60 days will be summarized as x/n (%) in each group together with two-sided 95% Wilson confidence intervals and corresponding confidence intervals for risk differences between groups.

The risk of the primary efficacy endpoint of new MRI-proven brain infarction or death by 60 days will be summarized in the same way. In addition, we will perform a linear trend test for group differences based on logistic regression with adjustment for gender, MRC grade, and age.

The risk of disability or death will be summarized as for the primary efficacy endpoint and the analysis of overall survival during 240 days will be based on Kaplan-Meier graphs and Cox regression. The frequency of adverse events in each study arm and resolution of CSF inflammation will be analysed descriptively.

Analyses to explore the effect of LTA4H genotype will include this information as an additional covariate in the regression models.

As this is a pilot study of relatively small size and limited power, p-values will be interpreted with caution and a one-sided p-value <0.1 will be regarded as mild evidence for an effect. Corresponding two-sided 95% confidence intervals will be provided for all tests to assess the range of plausible magnitudes of effects given the data.

No imputation of missing data will be performed. For the analysis of GI/cerebral bleeding by day 60, patients lost to follow-up before day 60 (without prior GI bleeding) will be excluded from the analysis to get a conservative estimate of the true proportion of bleeding in the aspirin groups. The analysis of the primary efficacy endpoint will exclude patients with missing baseline or follow-up MRI scans (except for prior death).

All analyses will analyze patients according to their randomized treatment group.

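### The grade 3–4/serious adverse event endpoint is an event count that is only described, so it yields no between-arm safety estimate; a per-patient proportion with the plan's existing intervals would

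*Protocol*

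**What the plan says.** The secondary endpoints in section 5.2 include "Number of grade 3&4 and serious adverse events by day 60 from randomisation". The synopsis lists the same item as "Grade 3&4 and serious adverse events by 60 days", without saying whether events or patients are counted. Section 8.3 fixes the recording window: events starting after the first dose and "before the end of study day 60 will be recorded in the CRF".

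For the analysis, section 9.2 says: "The frequency of adverse events in each study arm and resolution of CSF inflammation will be analysed descriptively". In the same section, bleeding is summarised as x/n (%) with Wilson 95% intervals and "corresponding confidence intervals for risk differences between groups". Primary efficacy is summarised the same way, and so is disability or death. The general promise in 9.2 is that "Corresponding two-sided 95% confidence intervals will be provided for all tests", and no test of adverse events is planned.

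The primary objective in section 4.1 is "To generate pilot data on the safety and efficacy of 81mg daily and 1000mg daily dose adjunctive aspirin compared to no aspirin".

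**The concern.** The objective is comparative, but for this endpoint the plan produces only one descriptive figure per arm. The promise of confidence intervals does not reach it, because that promise is attached to tests.

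The unit also matters. A total of events says little about how many patients were harmed, because one patient with several recurrences can move an arm's total. The total depends on how long patients live as well: a patient who dies contributes one serious event (section 8.1 makes death a seriousness criterion) and then stops contributing. Section 8.4 says "As serious adverse events and mortality are common in tuberculous meningitis", so neither feature is remote in this population.

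At stake is whether the pilot can give a plausible range for the excess of severe harm with each dose, which a designer of the definitive trial would want. The data for that are already being collected.

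**Working it through.** **Inputs from the protocol.** 40 patients per arm (9.1); events counted to day 60 (5.2); Wilson and risk-difference intervals for bleeding (9.2). The protocol gives no adverse event rate, no separate death rate and no measure of how events cluster within patients. Every rate in steps 2 to 4 is therefore an assumption.

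**1. The plan's own safety figures.** None is stated for this endpoint. The nearest are the bleeding figures in 9.1, which reproduce closely:
- P(0/40 at 1%) = 0.99^40 = 66.9% (stated 67%).
- P(1/40) = 40 × 0.01 × 0.99^39 = 27.0% (27%).
- P(0 or 1 of 80) = 80.9% (80%).
- P(3 or more of 40 at 10%) = 77.7% (78%).
- Wilson limits: 8.8%, 12.9%, 6.7% and 2.6% (8.8%, 12.9%, 6.8% and 2.5%).

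So the interval method proposed below is one the plan already applies at this sample size.

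**2. Repeat events.** Take two arms, each with 20 of 40 patients affected.
- Arm X: 20 patients with one event each = 20 events.
- Arm Y: 17 patients with one event and 3 with six: 17 + 3 × 6 = 35 events.
- Event ratio: 35/20 = 1.75. Risk difference in patients affected: 20/40 − 20/40 = 0.

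**3. Dependence on survival.** Let r be the non-fatal events per patient over a full 60 days and d the proportion dying. Assume deaths are spread evenly over days 0 to 14 (mean day 7) and each death counts as one event.
- Mean total per patient = r × [(1 − d) × 60 + d × 7]/60 + d.
- Proportion with any event, where non-fatal counts are Poisson = d + (1 − d)(1 − e^(−r)).

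| r | Total, d = 20% | Total, d = 40% | Any event, d = 20% | Any event, d = 40% |
|---|---|---|---|---|
| 0.5 | 0.61 | 0.72 | 51% | 64% |
| 1.5 | 1.44 | 1.37 | 82% | 87% |
| 3 | 2.67 | 2.34 | 96% | 97% |

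Each extra death changes the total by 1 − r × 53/60, so the sign turns at r = 60/53 = 1.13. With a constant death hazard instead and r = 1.5, raising mortality from 10% to 40% moves the total from 1.52 to 1.58. The direction is therefore not fixed. In this model the per-patient proportion always rises with mortality, though it flattens when events are very common.

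**4. What the per-patient version would deliver.** Newcombe interval from the Wilson limits (l, u), with difference D = p1 − p2:
- Lower limit = D − √[(p1 − l1)² + (u2 − p2)²].
- Upper limit = D + √[(u1 − p1)² + (p2 − l2)²].

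Wilson limits are 35.2% to 64.8% for 20/40 and 44.6% to 73.7% for 24/40.
- 20/40 v 20/40: 0 points (−20.9 to +20.9).
- 24/40 v 20/40: lower = 0.10 − √(0.154² + 0.148²) = −0.114; upper = 0.10 + √(0.137² + 0.148²) = +0.301. That is +10 points (−11.4 to +30.1).
- 28/40 v 20/40: +20 points (−1.4 to +39.0).

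These intervals are wide but interpretable, and the current plan provides none for this endpoint.

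**The case against.** The best defence is that this is a secondary endpoint in a 120-patient pilot. Descriptive adverse event tables are ordinary there, and their layout is commonly left to an analysis plan, which is not shown here. The word frequency in 9.2 can be read as patients affected, and the synopsis omits the word number. Bleeding is the chosen comparative safety measure and does get risk-difference intervals. Section 8.4 mentions common serious events as a reason to focus reporting on events relevant to the intervention, so all-cause totals may be mostly disease background. The binary version also loses information if nearly everyone has an event, as the last row of the table shows.

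Much of this stands and limits the weight of the point. It does not remove it: 5.2 fixes a number of events and 9.2 assigns description. These are stated choices rather than silence, and 9.2 does extend the fuller summary to another secondary outcome, disability or death.

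A reader might infer three stronger things that the documents do not support:
- That comparing totals would inflate the false-positive rate. A naive comparison that treated events as independent would (10% to 38% two-sided at an assumed mean of 1 to 2 events per patient and gamma dispersion of 0.5 to 2), but no such test is planned.
- That an arm with excess early deaths could pass as safe. Step 3 shows that the sign can go either way. Deaths by day 60 also enter primary efficacy with risk-difference intervals, and mortality is examined again in time to death and in disability or death.
- That the objective has no safety comparison, or that this endpoint carries most of it. Bleeding supplies one, and the protocol gives no adverse event rates from which to rank the two.

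**Conclusion.** The point holds in a limited form. As written, the endpoint is a count that is only described, so it contributes no between-arm estimate or interval to an objective framed as a comparison with no aspirin. Its total can also differ by a factor of 1.75 between arms with identical numbers of affected patients. That factor is a constructed example, not a prediction. The dependence on survival is real in principle, but its size and direction rest on rates the protocol does not give.

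No sample size or power figure is affected, and the protocol does not contradict itself here. The weight is minor to moderate: a better summary is available from data already collected, with methods already in the plan.

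**What to change.** - **Section 5.2:** define the endpoint as the number (%) of patients with at least one grade 3–4 or serious adverse event by day 60 from randomisation. Align the synopsis entry.
- **Section 9.2:** report it per arm with Wilson 95% intervals, and give risk differences with 95% intervals for each aspirin arm against placebo, as for bleeding.
- **Tables:** show deaths separately and keep event totals per arm as a supporting table.

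The cost is about one sentence in each section. No new data, visits or patients are needed. The downside is that repeat events appear only in the supporting table, and the proportion is less informative if nearly all patients have an event.

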# BACKGROUND AND RATIONALE

Tuberculous meningitis (TBM) is the most devastating form of tuberculosis, killing or maiming around half of all sufferers [^1^](#_ENREF_1). There are three broad approaches to improving outcome: earlier diagnosis and treatment with anti-tuberculosis chemotherapy (ATC), enhancing anti-microbial killing by optimising or improving standard ATC, and controlling the intra-cerebral inflammatory response. Studies performed nearly a decade ago at the Hospital for Tropical Diseases (HTD), Ho Chi Minh City, demonstrated how simple clinical and laboratory methods assist in early TBM diagnosis [^2-4^](#_ENREF_2) and that adjunctive corticosteroids reduce mortality from the disease [^5^](#_ENREF_5). The current HTD/OUCRU trial (05TB) examines the hypothesis that enhanced early bacterial killing with high-dose rifampicin and levofloxacin will increase survival from TBM [^6^](#_ENREF_6). The trial completed recruitment of 817 adults with TBM in June 2014.

This pilot study returns to the long-standing hypothesis that outcome from TBM can be improved by control of the intra-cerebral inflammatory response. Our previous randomised controlled trial of adjunctive dexamethasone in 545 adults with TBM found dexamethasone increased survival but had no impact on neurological disability [^5^](#_ENREF_5). Indeed, 5-year follow-up of trial patients found dexamethasone’s impact on survival was lost after around 2 years, primarily because of the deaths of the higher proportion of severely disabled patients in the dexamethasone treatment arm[^7^](#_ENREF_7). There is, therefore, an urgent need to explore ways to prevent the neurological sequelae of TBM which complement the effect of dexamethasone on survival. We hypothesise that aspirin will reduce neurological sequalae from TBM by enhancing the resolution of intra-cerebral inflammation and by preventing intra-vascular thrombosis and brain infarction.

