## Summary of Trial Design

The study is a parallel group, double blind, randomised, placebo controlled trial of 60 days of placebo vs. 81mg daily dose vs. 1000mg daily dose aspirin for the treatment of HIV-uninfected adults with tuberculous meningitis (see trial schema in appendix A). Patients will be recruited at the Hospital for Tropical Diseases (HTD), Ho Chi Minh City, Vietnam and should not have had more than 2 days of anti-tuberculosis chemotherapy or have received aspirin or any other NSAID within 2 weeks of randomisation. They should be able to have an MRI of their brain within 5 days of randomization.

Once enrolled, patients will be followed for 60 days and followed up at 8months for final outcome. They will all receive standard anti-tuberculosis chemotherapy and adjunctive dexamethasone (for 6-8 weeks), according to respective National Tuberculosis Programme guidelines (see attached guidelines for Viet Nam with this protocol). Participants will be stratified by site and MRC disease severity grade, and randomised on entry to one of three arms (1:1:1 ratio): aspirin 81mg, aspirin 1000mg or placebo daily for 60 days. Patients will be in-patients for at least the first 14 days of study treatment enabling real-time active surveillance of any adverse events after which they will be discharged according to clinical care. Study drug and standard treatment may be continued while patients are followed as out-patients.

Lumbar puncture will be performed before the start of treatment and then repeated in all patients on day 30 and 60 as per normal clinical care. Blood draws for pharmacokinetic assessment will be done 5 times between days 1 and 14. Assessment of peripheral blood monocyte/macrophage antimicrobial activity will be made at baseline and on day 240.

Clinical assessments will be performed at enrolment and weekly between day 7 and discharge. Brain magnetic resonance imaging (MRI) will be performed at baseline, day 60 and 240. A final clinical assessment of neurological disability will be made at 240 days.

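### The day-240 infarction endpoint omits the word *new*, so infarcts already on the baseline scan count as outcomes and dilute any treatment contrast

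*Protocol*

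**What the plan says.** Section 5.2 of the protocol sets the primary efficacy endpoint as "any new MRI-proven brain infarction or death by 60 days". The secondary list in the same section contains "The proportion of patients with MRI-proven infarction by day 240", and the synopsis (section 1) words it identically. Neither *new* nor *or death* appears in the day-240 endpoint, and no other section adds them.

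Section 5.1 schedules the scans: "Brain magnetic resonance imaging (MRI) will be performed at baseline, day 60 and 240". Appendix C scores infarct as one of the cerebral imaging criteria for diagnosing tuberculous meningitis.

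Section 9.2 says in general that "No imputation of missing data will be performed". Its only rule on scans and death is limited to one endpoint: "The analysis of the primary efficacy endpoint will exclude patients with missing baseline or follow-up MRI scans (except for prior death". Section 9.2 does not mention the day-240 infarction endpoint. Death has its own secondary endpoint in section 5.2: "Time to death during 240 days from randomisation".

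**The concern.** An infarct on the entry scan happened before treatment could act on it. If it counts as an outcome, it adds the same expected number of events to every arm. It also hides any new infarct in that patient, because the patient is already counted. Both effects pull the arms together. Because infarct is a diagnostic imaging feature in Appendix C, infarcts at entry are foreseeable.

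Death raises a second, conditional problem. The Background describes the disease as "killing or maiming around half of all sufferers". That is not a mortality rate, but it makes deaths before day 240 likely. A patient who dies with no follow-up scan has no observed post-baseline infarct status. Dropping such patients, or scoring them infarct-free, lets survival enter the comparison.

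At stake is the only late imaging result of a pilot meant to inform a larger trial. A diluted result could be read as a fading effect when it only reflects the definition.

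**Working it through.** **Plan's own figure.** None is given for the day-240 endpoint. Section 9.1 gives figures for the day-60 composite: 40% in the control arm, possibly 20% on 81 mg, 40 patients per arm, and power of about 75% (one-sided 10%) and 50% (one-sided 2.5%) for a three-group trend test. A two-arm normal approximation for 40% v 20% with 40 per arm gives 75.4% and 49.7%, so the figures are a usable anchor.

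**Assumptions.** The protocol gives neither baseline infarct prevalence *b* nor 240-day death and infarct rates. To match 40% v 20%, I assume deaths of 20% v 10% and new infarction in survivors of 25% v 11.1%.
- New infarction among all randomised: 0.80 × 0.25 = 20%; 0.90 × 0.111 = 10%.
- New infarction or death: 20 + 20 = 40%; 10 + 10 = 20%.

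For simplicity, patients who die have no new infarct on an earlier scan, and baseline and new infarction are independent.

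**Step 1: effect of omitting *new*.** A patient meets the literal endpoint with a baseline infarct, whether or not they later die, or with a new one. With *q* the risk of new infarction among all randomised:

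- proportion = b + (1 − b)q
- difference = (1 − b)(q_placebo − q_aspirin)

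| b | placebo | aspirin | difference |
|---|---|---|---|
| 0% | 20% | 10% | 10 points |
| 20% | 36% | 28% | 8 |
| 30% | 44% | 37% | 7 |
| 50% | 60% | 55% | 5 |
| 60% | 68% | 64% | 4 |

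At b = 30%: 0.30 + 0.70 × 0.20 = 0.44 and 0.30 + 0.70 × 0.10 = 0.37.

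Precision suffers too, because the proportions move towards 50%. Pairwise power at one-sided 10% with 40 per arm is Φ[(difference − 1.2816 × SE0)/SE1], where SE0 uses the pooled proportion and SE1 the separate ones.
- 20% v 10%: SE0 = 0.0798, SE1 = 0.0791, power 49%.
- 44% v 37%: SE0 = 0.1098, SE1 = 0.1095, (0.07 − 0.1407)/0.1095 = −0.65, power 26%.

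**Step 2: what handling of deaths could add.** At b = 30%, any infarct in survivors is 0.30 + 0.70 × 0.25 = 47.5% v 0.30 + 0.70 × 0.111 = 37.8%. Excluding deaths gives these figures. Scoring deaths infarct-free gives 0.80 × 47.5 = 38% v 0.90 × 37.8 = 34%. Other assumed death rates that keep the composite at 40% v 20% give a different picture:

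| deaths | new infarct in survivors | deaths infarct-free | deaths excluded |
|---|---|---|---|
| 20% v 10% | 25% v 11.1% | 38 v 34 | 47.5 v 37.8 |
| 20% v 20% | 25% v 0% | 38 v 24 | 47.5 v 30 |
| 30% v 10% | 14.3% v 11.1% | 28 v 34 | 40 v 37.8 |

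The third row reverses only when deaths are scored infarct-free. The protocol prescribes neither handling.

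**The case against.** Four objections deserve weight.

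1. *Incident infarction may be what was meant.* The Background describes a cited trial's endpoint, and the rationale poses one of the pilot's questions, in terms of MRI-proven infarction without *new*, in contexts about preventing stroke. A baseline scan also makes that reading natural. This is plausible, but section 5.2 uses *new* for the primary endpoint and omits it for this one, and an endpoint definition should not rest on inference.

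2. *Leaving out death is legitimate.* Time to death is a separate secondary endpoint, and section 9.2 also summarises disability or death. Infarction alone can therefore be a proper component. This stands: the missing *or death* is not in itself an error.

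3. *Handling of deaths may be settled in the statistical analysis plan,* which is not at hand. This also stands. I state only what would follow from two possible choices.

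4. *It is a secondary endpoint in a small pilot* whose p-values are to be read cautiously. True, and it limits the importance of the point.

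A reader might go further and infer that the wording can erase or reverse a real reduction in infarction. For example, assume 35% baseline prevalence, deaths of 30% v 15% and new infarction in survivors of 25% v 12%. Scoring every death infarct-free gives 0.70 × 51.25 = 35.9% v 0.85 × 42.8 = 36.4%. But that scores as infarct-free even patients whose baseline infarct meets the literal endpoint. Counting those infarcts gives 35.9 + 0.30 × 35 = 46.4% v 36.4 + 0.15 × 35 = 41.6%. The difference is (0.175 − 0.102)(1 − b) = 0.073(1 − b), which is diluted but never reversed by baseline prevalence. Nor does a death before day 240 rule out an event: the endpoint runs *by* day 240, so an infarct on the day-60 scan still counts.

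**Conclusion.** The point holds as a definitional defect. As written in sections 1 and 5.2, the day-240 endpoint counts infarcts that precede treatment, and any difference in new infarction shrinks by the factor (1 − baseline prevalence). At an assumed 30% prevalence, 10 points become 7, and pairwise power at one-sided 10% falls from about 49% to 26%. These figures rest on assumed rates and on independence of baseline and new infarction; the direction (dilution) does not depend on the particular rates.

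Distortion by survival is possible but conditional. It arises only if deaths without a follow-up scan are dropped or scored infarct-free, and its size and direction depend on death rates that the protocol does not give. The documents do not support the claim that the wording itself makes a benefit vanish or reverse. The primary endpoint and its conclusion are untouched. The change is worth making, but it is not critical.

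**What to change.** In sections 1 and 5.2, define the endpoint as new MRI-proven brain infarction compared with the baseline scan, by day 240. State that a new infarct on the day-60 scan counts even if the patient dies before day 240.

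Report it beside the composite of new infarction or death by day 240. Extend to that composite the rule that section 9.2 gives for the primary endpoint: exclude patients with a missing baseline or follow-up scan unless they died earlier. A survival difference is then visible alongside the infarction result.

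The cost is wording in sections 1, 5.2 and 9.2. Scans at baseline, day 60 and day 240 are already scheduled and deaths are already recorded, so no new procedure or visit is needed.
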